#### Secondary outcomes

Maternal:

Admission to hospital for symptoms of threatened preterm labourAdministration of antenatal corticosteroids for fetal lung maturationAdministration of magnesium sulphate for fetal cerebral protectionTransfer to other hospitals for neonatal cot availability (*in utero* transfer)Time between intervention and deliveryRequirement for additional emergency/rescue cerclageSerious complications occurring due to trial intervention: bladder injury, bowel injury, intraoperative rupture of membranes, cervical tear, hysterectomyMaternal sepsisAdmission to ITUMaternal death

Neonatal:

Gestation at birthBirthweightApgar scores (if available)Days before discharge home (up to 28 days)Admission to neonatal unitNeonatal infectionAny baby death

 ◦ *In utero* fetal death at or after 14 weeks◦ Stillbirth◦ Neonatal death

### Data collection

Data will be collected by attending clinician or research midwives and includes: at randomisation - participant background: demographic characteristics, risk factors, obstetric history; before pregnancy trial intervention procedure (Group B – TAC); during pregnancy - trial intervention procedures (Group A - TVC or TAC, Group B – TVC); clinical care: preterm surveillance methods and test results, e.g. infection screening, cervical length measurements, caesarean section scar characteristics, predictive biomarker tests, concomitant treatments; after pregnancy - outcomes: e.g. onset of labour, gestation at delivery, infection, admission to ITU (mother) and/or neonatal unit (baby).

Data will be stored on the ABOVE Trial Database, which is hosted within the already established PCN Database (www.medscinet.net/ukpcn). This is a secure web-based platform containing standardised clinical information regarding women at high risk of sPTB. The ABOVE database’s data monitoring facility will be used to ensure data quality [10]. This function allows efficient and remote raising and answering of queries by the central and site trial teams.

The data collected will allow us to evaluate the effectiveness of the interventions on preventing poor outcomes, whether there are differences between women from different groups (demographic characteristics and risk factors) and whether treatment effects are compounded by other variables, such as intensity of preterm surveillance and concomitant treatments.

### Data analysis

A data analysis plan has been prepared prior to commencement of study recruitment. Maternal, pregnancy, and surgical procedure characteristics will be presented with counts and percentages for categorical variables, mean and standard deviation for continuous Gaussian distributed variables, and median and interquartile range for continuous non-Gaussian variables.

All primary and secondary outcomes, and the components of the primary outcome will be summarised by treatment arm and Group (A or B) using frequencies and percentages.

In addition, relative risk will be calculated for the treatment effect (TAC vs. TVC) with 95% confidence intervals. An interaction test will be carried out to examine whether the treatment effect is significantly different between groups A or B. Where a difference is detected, separate relative risks will be presented for both groups. Where there is a significant treatment effect, Risk differences and Number Needed to Treat (NNT) will also be presented, with confidence intervals if significant. All these analyses will be corrected for the minimisation variable and Group (A or B).

The primary analyses will be by modified intention-to-treat for the pre-conception trial arms. Women who did not conceive, suffered an early miscarriage or are lost to follow-up will be excluded. A TVC will not be inserted in a non-pregnant patient (in line with standard clinical care) and therefore these participants will be removed from the trial, at the end of the 18-month recruitment period, so that the results relate to the number of stitches actually placed.

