### Power calculation

A sample size estimation on data utilised data from a previous observational study performed by our group. This calculated that calculated that a TAC should provide a relative risk reduction of 67% for PTB < 30 weeks compared to TVC in this high-risk cohort of women (unpublished data). A total of 40 women in each intervention group (TAC/TVC) is required for 80% power, at 5% significance level, to show a significant difference between the two groups. This would equate to a total of 160 women in the study; 40 x group TVC vs. 40 x TAC in both groups: Group A (in pregnancy) and Group B (prior to pregnancy). The recruitment target accounts for a potential drop-out rate of 50% of Group B participants who may not have a subsequent pregnancy after randomisation; as informed by the MAVRIC trial [7].

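### The rule that all outcomes are summarised as frequencies and percentages does not fit five continuous, count or ordinal secondary outcomes

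*Protocol article*

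**What the plan says.** The Data analysis section of the protocol article sets out three layers.

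- **Characteristics.** "Maternal, pregnancy, and surgical procedure characteristics will be presented with counts and percentages for categorical variables, mean and standard deviation for continuous Gaussian distributed variables", followed by median and interquartile range for non-Gaussian variables. This is the only place where continuous summaries are named, and it covers characteristics.
- **Outcomes, descriptive.** Every primary and secondary outcome, with the parts that make up the primary one, "will be summarised by treatment arm and Group (A or B) using frequencies and percentages".
- **Outcomes, treatment effect.** "In addition, relative risk will be calculated for the treatment effect (TAC vs. TVC) with 95% confidence intervals". Where there is a significant effect, "Risk differences and Number Needed to Treat (NNT) will also be presented". These analyses are corrected for the minimisation variable and Group.

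The Secondary outcomes section lists one maternal item on a time scale (time between intervention and delivery) and, among the neonatal items, gestation at birth, birthweight, Apgar scores and "Days before discharge home (up to 28 days"). None is given bands or a cut-point.

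The Data analysis section also records that "A data analysis plan has been prepared prior to commencement of study recruitment". That plan is not at hand.

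**The concern.** A percentage of birthweight or of gestation does not exist until the measurement is put into categories. The outcome sentence is universal and makes no exception for numeric outcomes, although the sentence before it separates categorical from continuous variables for the characteristics. Followed literally, it means that five listed outcomes are reduced to categories, and the article then names no effect measure that could use their original scale.

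Categorising a measured outcome generally makes the comparison less precise. In a trial of 160 women the graded outcomes, gestation at birth above all, are a natural complement to a primary outcome that cuts gestation at 30 weeks. A secondary analysis that cuts gestation again would give up much of what the graded measure adds.

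**Working it through.** **Step 1. Compare the list with the rule.**

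| Secondary outcome | Scale | Bands or cut-point stated | Suits percentages and relative risk as listed |
|---|---|---|---|
| Time between intervention and delivery | continuous | none | no |
| Gestation at birth | continuous | none | no |
| Birthweight | continuous | none | no |
| Days before discharge home | count, capped at 28 | none | no |
| Apgar scores | ordinal | none | only if banded or tabulated by score |
| Most other listed items (such as admissions, treatments given, complications, deaths) | occurrence | not needed | yes |

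The stated rule therefore misfits five outcomes. It suits the primary outcome, which is binary.

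**Step 2. Numbers of women.** The article gives no figure for the loss from categorising, so there is none to reproduce on that point. The size used here comes from the Power calculation section: "A total of 40 women in each intervention group (TAC/TVC) is required for 80% power, at 5% significance level". It applies in each of two Groups, so a Group-adjusted comparison has 2 × 40 = 80 per arm.

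The 40 can be reproduced only with an assumed control rate, because that section states none. Taking 41% from the Background and the stated 67% relative reduction:

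- p₁ = 0.41, p₂ = 0.41 × 0.33 = 0.1353, mean p̄ = 0.2727
- n = [1.960 √(2p̄(1−p̄)) + 0.842 √(p₁(1−p₁) + p₂(1−p₂))]² / (p₁−p₂)², which rounds up to 41 per arm, with power 0.799 at 40

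Control rates of 40% to 43% give 42 to 38 per arm. The planned size is taken as given below and has no bearing on whether the rule fits.

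**Step 3. Information kept by a binary cut (illustration).** Assume a normal outcome cut at quantile q. Relative efficiency against the uncut comparison of means is φ(z_q)² / [q(1−q)], where φ is the standard normal density.

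| Cut at | Efficiency | 80 per arm act like |
|---|---|---|
| median: 0.3989² / 0.25 | 0.637 (= 2/π) | 80 × 0.637 = 51 |
| 20th percentile | 0.490 | 80 × 0.490 = 39 |
| 10th percentile | 0.342 | 80 × 0.342 = 27 |

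**Step 4. The same in terms of power.** With 80 per arm, the shift that a comparison of means detects with 80% power (two-sided 5%) is (1.960 + 0.842) × √(2/80) = 0.443 SD. Comparing proportions for that same shift gives the following power. Each range covers placing the cut at the quantile in one arm or midway between the arms.

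- median: 0.595 to 0.603
- 20th percentile: 0.429 to 0.490
- 10th percentile: 0.293 to 0.362

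**The case against.** The strongest reply is that this is loose wording in a condensed article, and that the method for each secondary outcome belongs in the analysis plan. Several parts of that reply stand.

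- **Scope of the relative risk.** A reader might infer that the article promises relative risks for every secondary outcome. It does not say so. The word all governs only the descriptive sentence, and the relative-risk sentence names no outcomes. Its scope is inferred from its position and from the absence of any other measure; it may be meant only for outcomes where a relative risk is defined.
- **Cut-points chosen later.** A reader might infer that thresholds are left open to choice in an unblinded trial. The documents do not support this. The analysis plan was prepared before recruitment, and any bands may be fixed there.
- **Binary cuts.** Percentages can describe several ordered bands, such as gestation bands or Apgar scores, so a single cut at one point does not follow from the text.
- **A larger loss.** One could say that 40 women per arm act like about 25 (40 × 0.637 = 25.5). That is the size within one Group. The default analysis estimates one effect corrected for Group, and gives separate relative risks only if the interaction test detects a difference.
- **Normality.** Days to discharge are capped at 28, and gestation in a cohort with substantial early loss is unlikely to be normal. For such outcomes the loss may be smaller, or may even reverse.

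The reply does not dispose of the point, because the article is not silent. It gives a rule for all outcomes that five of them do not fit. If the analysis plan treats them on their own scale, the article misreports it. If the plan follows the article, information is likely to be lost. One could stretch pregnancy characteristics to include gestation or birthweight, but that would clash with the next sentence and would still supply no effect measure.

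**Conclusion.** The point holds as a misstatement limited to secondary outcomes. The summary rule fits the binary outcomes and misfits five others, and every effect measure named is for binary data. The primary outcome, the sample size and the main conclusion of the trial are unaffected, so this is a minor, worthwhile improvement.

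The size can only be illustrated: about 36% of the information lost for a normal outcome split at the median, so 80 per arm act like about 51. This rests on normality, a single cut at the median and the planned 160 women with complete data. No cut is stated in the article, so the figure describes what following the sentence could cost, not an analysis known to be planned.

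**What to change.** 1. Limit the sentence on frequencies and percentages, and the one on relative risk, to binary and categorical outcomes.
2. For gestation at birth, birthweight, time between intervention and delivery, days before discharge home and Apgar scores, report mean (SD) or median (IQR) by arm and Group. Add a treatment effect on the original scale with 95% CI, corrected for the minimisation variable and Group. An adjusted mean difference would suit birthweight; a rank, ordinal or time-to-event method would suit skewed, capped or ordinal outcomes. These are examples, and other sound choices exist.
3. Reconcile the text with the existing data analysis plan. If that plan already fixes bands or continuous methods, the article need only say so. If a time-to-event method is used, the plan should also say how deliveries that are not spontaneous are handled.

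The cost is about two sentences and standard analyses of data already being collected. The primary analysis does not change.

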## Background

There is increasing evidence that prior pregnancies ending with delivery by in-labour caesarean (CS) are associated with both spontaneous preterm birth(sPTB), i.e. delivery < 37 weeks completed gestation, and mid-trimester loss (MTL), i.e. pregnancy loss between 14 and 24 weeks, in subsequent pregnancies. A retrospective analysis of US cohort data demonstrated that full dilatation CS (FDCS) is associated with a six-fold increased risk of sPTB compared to first stage CS [1]. Adding to this concern is the high risk of a recurrent sPTB in this group of women [2, 3]. A recent study reported that the relative risk (RR) of recurrent sPTB at < 37 weeks gestation is 2.7 for all emergency caesarean sections (EMCS) and 3.1 for a full dilatation CS (FDCS), when compared to women with a prior sPTB and without EMCS as a risk factor [2]. This risk further increases when including MTL as an outcome, with 25.4% delivering at < 24 weeks of gestation (RR 5.65) [2]. Another study demonstrated a 41% absolute risk of recurrence of sPTB at < 30 weeks of gestation [3].

The relationship between sPTB, MTL and in-labour caesarean may be related to inadvertent cervical damage at the time of CS (cervical caesarean damage, CCD). At the time of in-labour caesarean, the surgical incision itself, or surgical site extensions, may be near or within the cervical tissue. This could disrupt the integrity of cervical tissue, leading to a cervical scar defect and resulting in compromised cervical function in future pregnancies [4]. The extent of CCD may also be influenced by the suture material at the time of caesarean section, the healing process and incidence of post-operative infection.Treatment modalities to reduce sPTB are currently limited but include cervical cerclage insertion [5]. There are three options for prophylactic suture placement: low vaginal or high vaginal cervical sutures (known as transvaginal cerclages - TVCs) or transabdominal cerclage (TAC). TVCs are placed during pregnancy, while TACs, placed at the level of the internal os, require laparotomy or laparoscopy either prior to pregnancy or in pregnancy [6]. In the UK, TACs are usually reserved for women who have had a trachelectomy or a failed vaginally placed cerclage, where they are known to be highly efficacious [6].

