Treatment modalities to reduce sPTB are currently limited but include cervical cerclage insertion [5]. There are three options for prophylactic suture placement: low vaginal or high vaginal cervical sutures (known as transvaginal cerclages - TVCs) or transabdominal cerclage (TAC). TVCs are placed during pregnancy, while TACs, placed at the level of the internal os, require laparotomy or laparoscopy either prior to pregnancy or in pregnancy [6]. In the UK, TACs are usually reserved for women who have had a trachelectomy or a failed vaginally placed cerclage, where they are known to be highly efficacious [6].

TVCs are widely used to prevent sPTB in high-risk women [6]. However, retrospective studies show that they are ten-fold less effective in women who have had a sPTB following an in-labour CS, compared to other high-risk groups, with failure rates of 46% [4]. Conversely, TAC has a success rate of > 90% in high-risk women [7]. Another retrospective cohort study demonstrated that TAC was associated with less sPTB at < 30 weeks compared to TVC [8]. Moreover, women with a history of preterm birth and mid-trimester pregnancy loss report having a TAC in place reassuring [9].

Efficacy of TAC is thought to be related to the position of the suture above the scar. In pregnancy this may not be possible due to the implantation site and the inherent dangers of inserting a suture near the embryonic sac. Furthermore, increased vascularity in the pregnant cervix and an enlarged gravid uterus can make suture placement difficult. To date, there has been no comparison of outcomes from preconception and in-pregnancy TAC procedures.

In response to the accumulating, but often retrospective, evidence associating in-labour CS with MTL and sPTB, we have designed the ABOVE randomised control trial (RCT) to address this by comparing the effectiveness of TAC versus TVC in women who have had a previous sPTB or MTL following in-labour caesarean, both before and during pregnancy.

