### Design

ABOVE is a multicentre RCT comparing TAC and TVC as a preventative strategy for sPTB in women with history of an in-labour CS and subsequent MTL (between 14^+ 0^-23^+ 6^ weeks’ gestation) or sPTB (< 30 weeks’). Participants will be allocated to one of two groups - Group A (already pregnant) and Group B (planning a pregnancy) - and randomised 1:1 to TAC or TVC within each group. It is important to separately evaluate pre-conception and in-pregnancy TACs, as the suture can be placed higher pre-pregnancy and this may provide better support around cervical weakness caused by CCD. Therefore, the trial is separately powered for these two groups, and will require complete data from 160 participants (*n* = 80 in Group A, *n* = 80 in Group B).

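### The trial is sized as two separate TAC v TVC comparisons, but the analysis leads with a pooled relative risk and lets an interaction test decide whether the group results are presented

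*Protocol article*

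**What the plan says.** All references are to the protocol article.

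- **Design.** Allocation is "randomised 1:1 to TAC or TVC within each group". The section argues that pre-conception and in-pregnancy TAC need separate evaluation, and concludes: "Therefore, the trial is separately powered for these two groups, and will require complete data from 160 participants".
- **Power calculation.** "A total of 40 women in each intervention group (TAC/TVC) is required for 80% power, at 5% significance level". The effect assumed is a "relative risk reduction of 67% for PTB < 30 weeks compared to TVC", and the 40 v 40 is applied once in Group A and once in Group B.
- **Data analysis.** Counts and percentages are tabulated by arm and Group. The treatment effect is one TAC v TVC relative risk with a 95% confidence interval, corrected for Group and for the minimisation variable. Then: "An interaction test will be carried out to examine whether the treatment effect is significantly different between groups A or B". Separate relative risks are given for the two groups only where that test finds a difference. Risk differences and numbers needed to treat are added wherever the treatment effect is significant. No level is given for the interaction test.

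The article says that an analysis plan was prepared before recruitment. That plan was not available for this review.

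**The concern.** Design and Power calculation make the two group comparisons the questions that the trial must answer. Data analysis makes the pooled comparison the default and shows the group relative risks only after a significant interaction. Both cannot define the primary result.

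Two consequences follow. First, choosing the contrast by a test on the same data opens a second route to a significant result. When the interaction is positive by chance, the two groups have drifted apart, so at least one of them is often extreme. Secondly, 40 per arm was chosen to detect an effect within a group, not a difference in effect between groups. The gate can therefore stay shut when one group shows the effect that the trial was sized to detect.

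**Working it through.** **1. The plan's own figure.** Inputs: two-sided 5% (sidedness is not stated; assumed from the 95% intervals), 80% power, and relative risk 1 − 0.67 = 0.33. The Power calculation gives no TVC event rate. I assume 41%, from the Background: "Another study demonstrated a 41% absolute risk of recurrence of sPTB at < 30 weeks of gestation". Then pC = 0.41, pT = 0.41 × 0.33 = 0.1353 and mean p = 0.2727.

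n per arm = [1.96·√(2·p(1−p)) + 0.8416·√(pC(1−pC) + pT(1−pT))]² / (pC − pT)² = (1.2343 + 0.5042)² / 0.2747² = 40.05.

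Power at exactly 40 per arm is 79.9%. At 46%, the TVC failure rate also given in the Background, n is 34. So 40 per arm is the size of one within-group comparison at the full 5%.

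**2. False claims under the rule in Data analysis, normal theory.** With no effect in either group and equal group sizes, Z_A and Z_B are independent standard normal. Pooled Z = (Z_A + Z_B)/√2 and interaction Z = (Z_A − Z_B)/√2, and these two are independent. Take the interaction at 5% (assumed).

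- Interaction not significant, pooled significant: 0.95 × 0.05 = 0.0475.
- Interaction significant and Group A or B significant at 5%: 0.0325 by numerical integration, which is 0.0325/0.05 = 65% of the trials with a chance interaction.
- Total: 0.0475 + 0.0325 = 0.080.

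With the interaction at 10% the total is 9.4%; at 20% it is 10.8%. If Group B is half the size of Group A it is 8.1%. Counting only false claims that favour TAC, the rule gives 4.1% against a nominal 2.5%.

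**3. Small-sample check.** Binomial simulation with 40 per arm per group and Wald tests on the log relative risk:

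| Event rate, all arms | Rule in Data analysis |
|---|---|
| 20% | about 5.6% |
| 30% | 6.5% |
| 41% | 6.9% |

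The Wald test is conservative here: at 41% the pooled test alone runs at 4.1%, so the rule still gives 6.9/4.1 = 1.7 times the rate of a single test. Score-type tests give about 8%.

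**4. What the gate withholds.** Assume 41% v 41% in Group A and 41% v 13.5% in Group B, with the interaction tested on the log relative risk at 5%.

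- Interaction significant: 59% of trials.
- Group B significant in favour of TAC but interaction not significant: 21% if Group B is tested by Wald log relative risk, 24% if by a score test.

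A single result shows why. If Group B has p = 0.04 (Z = 2.05), the interaction is significant only if Z_A is below 2.05 − 1.96 × √2 = −0.72. Group A would have to point clearly the other way.

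**5. The design as sized.** Groups A and B each at 5%: 1 − 0.95² = 9.75% chance of at least one false claim. With Holm over the two groups at a 41% TVC rate, simulated power is about 78% per group if TAC works in both. If it works in one only, power at two-sided 2.5% with 40 per arm is 71% (79% at a 46% TVC rate).

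**The case against.** **The analysis plan is not shown.** An alpha split, a testing order and the interaction level are usually set there, so their absence from an article is no fault. That stands, and none of it is counted here. What remains is what the article states: a sizing built on two group comparisons, and a data-dependent rule that makes those comparisons conditional.

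**The size can be overstated.** A reader might infer that pooled, Group A and Group B results can each be claimed at 5%, so that the error rate is 8% to 12% against a promised 5%. The document does not support this. The upper end (11.5% by normal theory) needs a group claim whatever the interaction shows, which Data analysis does not provide for. The 5% in Power calculation is a per-comparison sizing level; no rate over all claims is promised. The 8% itself assumes an interaction level and falls to about 6% to 7% with Wald relative risk tests. All of this stands and limits the point.

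**Two populations, two questions.** Groups A and B do not overlap, are randomised separately and differ in TAC timing. Testing each at 5% is a recognised position, so a multiplicity correction is not obligatory. That also stands. It argues for always reporting the two group results, which the interaction gate prevents.

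**Nothing is hidden.** Counts by arm and Group are tabulated regardless. True, but the relative risk and its interval, the estimate on which a group conclusion would rest, depend on the gate.

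**Conclusion.** The point holds as a conflict between sections with measurable consequences. Design and Power calculation fix two group comparisons; Data analysis fixes a pooled one and lets an interaction test bring the group relative risks in or leave them out.

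False claims under no effect rise from 5% for one pre-named contrast to about 8% by normal theory, or about 6% to 7% with Wald log relative risk tests at event rates of 20% to 41%. About 4% are false claims favouring TAC, against 2.5%. These figures assume two-sided tests and an interaction level of 5%. The inflation is modest.

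The loss on the other side is at least as important. Where TAC works only in Group B, roughly one trial in four or five would have a significant Group B result whose relative risk the plan does not present. That figure also rests on the assumed 41% TVC rate and the stated 67% reduction.

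**What to change.** In Data analysis:

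1. Name the Group A and Group B TAC v TVC relative risks for the primary outcome as the two primary contrasts, both always reported with 95% confidence intervals.
2. Label the pooled relative risk and the interaction test as supportive, with no role in choosing which contrast is tested or presented.
3. State whether the 5% applies to each group as a separate question, accepting about a 9.75% chance of at least one false claim, or to both groups jointly.

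If the joint option is chosen, Holm is suitable: the smaller p against 0.025, then the other against 0.05. Power calculation should then be restated, with its TVC rate. At an assumed 41%, power is about 78% per group if TAC works in both and about 71% if in one only.

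The cost is a paragraph of wording, settled before outcome data are seen, and a slightly lower stated power under the joint option. No extra patients are needed.

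### The two groups are powered separately, but their own relative risks are presented only if an unpowered interaction test is positive

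*Protocol article*

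**What the plan says.** Three sections of the protocol article bear on this.

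- **Design.** "It is important to separately evaluate pre-conception and in-pregnancy TACs", because a suture placed before pregnancy can sit higher. Women are "randomised 1:1 to TAC or TVC within each group". The section concludes: "Therefore, the trial is separately powered for these two groups", with complete data needed from 80 women in each.
- **Power calculation.** The effect assumed is that "a TAC should provide a relative risk reduction of 67% for PTB < 30 weeks compared to TVC", one value for both groups. Forty women per arm "is required for 80% power, at 5% significance level, to show a significant difference between the two groups". This is applied once in Group A and once in Group B, giving 160.
- **Data analysis.** A TAC v TVC relative risk with 95% confidence interval is calculated, corrected for the minimisation variable and for Group. An interaction test then asks whether the effect differs between A and B. "Where a difference is detected, separate relative risks will be presented for both groups". A second condition follows for absolute effects: "Where there is a significant treatment effect, Risk differences and Number Needed to Treat (NNT) will also be presented". Frequencies and percentages by arm and Group are given in every case.

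**The concern.** The sample size was set by two within-group comparisons, yet the analysis makes their estimates depend on a test for which the trial was not sized. An interaction between two groups of 80 is estimated much less precisely than the effect within either group, so the condition will often fail even when the groups truly differ.

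If the effects do differ, which is the protocol's stated reason for having two groups, the likely headline is a single averaged relative risk. A non-significant interaction could then be read as evidence that the timing of TAC does not matter. If the effects are alike, the reader still does not receive the two adjusted estimates for which the women were recruited.

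**Working it through.** **Inputs.** From the Power calculation section: 40 per arm per group, relative risk 0.33 (a 67% reduction), 5% significance, 80% power. That section gives no TVC risk, so two figures from the Background are used as assumptions: 41% (recurrence before 30 weeks) and 46% (TVC failure after in-labour caesarean). The level of the interaction test is not stated; two-sided 5% is assumed.

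**Step 1: the plan's own figure.** Two-proportion test, pooled variance, two-sided 5%.

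- 41% v 0.33 × 41% = 13.5%: 41 per arm needed; power at 40 per arm is 79.9%.
- 46% v 0.33 × 46% = 15.2%: 34 per arm needed (41 with continuity correction); power at 40 per arm is 86.3%.

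So 40 per arm is reproduced as a within-group sample size. Pooling the groups (80 v 80) gives about 98% power at a 41% TVC risk, so 160 is not the size that a pooled primary comparison would need.

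**Step 2: precision of the interaction.** For each arm, var(log risk) = (1 − p)/(40p). The interaction is the difference between two log relative risks, so its variance is the sum over four arms. At a TVC risk of 41%, with a relative risk of 0.67 in A and 0.33 in B:

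- each TVC arm (41%): 0.0360
- TAC in A (27.5%): 0.0660
- TAC in B (13.5%): 0.1598
- SE = √(0.0360 + 0.0360 + 0.0660 + 0.1598) = 0.546
- difference = ln(0.67/0.33) = 0.708
- power = Φ(0.708/0.546 − 1.96) + Φ(−0.708/0.546 − 1.96) ≈ 25%

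**Step 3: chance that the separate relative risks are presented.** Same formula throughout:

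| True RR in A | True RR in B | TVC risk 41% | TVC risk 46% |
|---|---|---|---|
| 0.33 | 0.33 | 5% | 5% |
| 0.50 | 0.33 | 11% | 12% |
| 0.67 | 0.33 | 25% | 29% |
| 1.00 | 0.33 | 57% | 64% |

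The first row is the design assumption; its 5% is simply the false-positive rate of the test. A simulation of 200,000 trials gave 3% for the first row at both TVC risks, 23% and 27% for the third, and 59% and 67% for the last.

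**Step 4: difference needed for 80% interaction power.** Hold Group B at 0.33 and the TVC risk at 41%, and recompute the SE as Group A changes. A ratio of relative risks of about 4.1 is needed. That puts Group A at 0.33 × 4.1 ≈ 1.35, where TAC would be worse than TVC.

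**The case against.** Several points on the other side stand.

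- **The group data are not hidden.** A reader might infer that the group results go unreported. They do not: outcomes are always tabulated by arm and Group, and a crude relative risk and interval follow from those counts. What is conditional is the adjusted, pre-specified estimate.
- **The pooled relative risk is a legitimate target.** The first objective in the Aim section concerns all eligible women, and the power calculation assumes one effect for both groups. If that holds, the pooled estimate is the more precise summary. To say that it describes neither group assumes a difference that the sample size does not. With relative risks of 0.33 and 0.67 and a 41% TVC risk, the pooled value of about 0.50 has an approximate 95% interval of 0.30 to 0.83, which covers both.
- **The scenarios are assumptions.** No section supports 0.67 for Group A. If the interaction were tested at 10%, power in that case would be about 37% rather than 25%. Power exceeds one half when TAC has no effect in one group and its full effect in the other.
- **The second objective is a different contrast.** It compares TAC before pregnancy with TAC in early pregnancy, across groups. It should not be read as a TAC v TVC result that this rule withholds.
- **The condition on risk difference and NNT is minor.** The overall relative risk is given with its interval whatever its significance, so a null result still carries its uncertainty.

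None of this removes the conflict. If the pooled comparison is primary, the statement that "the trial is separately powered for these two groups" and the derivation of 160 do not describe the primary analysis. If the group comparisons are primary, their estimates cannot depend on the interaction test.

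**Conclusion.** The point holds as a contradiction between stated rules. The Design and Power calculation sections set up two within-group comparisons; the Data analysis section presents their relative risks only after a positive interaction test that is powered nowhere in the document. Under the design assumption they would be withheld in about 95% of trials, and in at least 71% of trials when Group A has a relative risk of 0.67 or lower (but no lower than 0.33) and Group B 0.33. Presentation becomes more likely than not only when the groups differ about as much as no effect v full effect.

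These figures rest on a TVC risk of 41% to 46%, 40 women with complete data per arm per group, and a two-sided 5% interaction test. The conclusion is the same at either TVC risk. A reader might go further and infer that the group-specific comparisons must be made primary and the pooled one demoted. The documents do not settle that: the article does not name a primary comparison, and two primary 5% tests would carry a family-wise error of 1 − 0.95² = 9.75% unless handled.

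**What to change.** In the Data analysis section, and in the data analysis plan to match:

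1. Delete the condition on detecting a difference. Always present the TAC v TVC relative risk with 95% confidence interval within Group A and within Group B, each adjusted for the minimisation variable.
2. Report the interaction as a ratio of relative risks with 95% confidence interval, whatever its p-value.
3. State whether the group-specific or the pooled comparison is primary, with multiplicity handling if both groups are primary, so that Design, Data analysis and Power calculation agree.
4. As a minor addition, present risk differences with 95% confidence intervals regardless of significance.

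The cost is wording and a little extra analysis, with no new data or participants. The price is wider intervals for the group estimates: at a 41% TVC risk and a relative risk of 0.33, the unadjusted within-group interval is exp(ln 0.33 ± 1.96 × √(0.0360 + 0.1598)), about 0.14 to 0.79.
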